### Recruitment {15}

Identification, screening, and consent procedures will be undertaken by the PI, sub-investigator, and collaborator who will be trained and competent to participate according to the ethically approved protocol, principles of Good Clinical Practice (GCP), and the Declaration of Helsinki. We implanted a multi-faceted approach to ensure an adequate enrollment of participants to reach our target sample size. First, we displayed informational posters in participating institutions to enhance the patient awareness of the trial. Second, we held lectures for local family physicians to explain the nature and objectives of the trial. Last, we conducted public lectures to educate the general public about EGJOO and the specifics of this trial. This comprehensive strategy was designed to facilitate a broad understanding and encourage enrollment in the trial. The recruitment period has been designed for 2 years. The number of eligible patients per institution in a month is estimated to be approximately one. Assuming a 50% consent rate, the enrollment is expected to be completed in 2 years.

## Assignment of interventions: allocation

### Sequence generation {16a}

The allocation manager will prepare the allocation chart of investigational drugs (300 mg/day group, 600 mg/day group, or placebo group) and randomly assign participants to each group with a 1:1:1 allocation using the substitution block method stratified by institution. The allocation manager assigns participants to each group randomly using a computer-generated allocation table for the investigational drug (300 mg/day group, 600 mg/day group, or placebo group), employing a stratified blocked randomization method stratified by the institution, with a 1:1:1 allocation ratio.

### Allocation concealment mechanism {16b}

The allocation manager will conceal the allocation chart immediately after the completion of the allocation and keep it in a sealed envelope until the key is opened. In addition, the manager will prepare the emergency key code, which is stored and managed in the electronic data capture (EDC) system. The key code should not be opened except in accordance with the predetermined procedure.

### Implementation {16c}

The PIs or sub-investigators will confirm that the participants meet all the inclusion criteria and do not meet any of the exclusion criteria. The investigators will then obtain the identification code for the participants and register the participants using a web-based registration system. Upon the completion of registration, “eligible” participants will be assigned a drug number. The investigators will prescribe the investigational drug with the drug number obtained from the web registration system to that participant. The study will be terminated and appropriate measures will be taken for “non-eligible” participants.

## Assignment of interventions: blinding

### Who will be blinded? {17a}

This is a double-blind trial. Both the research staff and participants will be blinded. All data will be managed, evaluated, and statistically processed by a third party following the clinical research. Outcome evaluators will not be informed of the group of belonging. Data analysts will work on the final dataset where the group condition will be masked.

### Procedure for unblinding if needed {17b}

The PIs and sub-investigators may request the coordinating investigator to open the emergency key code if deemed necessary to identify the dose groups of the investigational drug to treat a participant in a medical emergency, such as the occurrence of a serious adverse event. Upon receiving the request, the coordinating investigator will consult with the allocation manager as necessary and determine the measures. If the coordinating investigator decides to open the code, the coordinating investigator will immediately request that the allocation manager open the code and receive a report on the dose group to which the investigational drug has been allocated. If possible, the PI or sub-investigator will send a report about the safety and efficacy of the investigational drug before opening the code. The coordinating investigator will then report the result of opening the code to the PI or sub-investigator. The coordinating investigator will record and maintain the process.

## Data collection and management

### Plans for assessment and collection of outcomes {18a}

Data will be collected at the following time points:T-1: Pre-enrollment observation period: seven consecutive days within 10 days prior to enrollmentT0: EnrollmentT1: During treatment period 1: days 1–28 of treatment period 1T2: After 4 weeks of treatment period 1 (scheduled visit): days 29–32 of treatment period 1T3: During treatment period 2: days 1–28 of treatment period 2T4: After 4 weeks of treatment period 2 (scheduled visit): days 29–32 of treatment period 2T5: During the post-treatment observational period: days 1–14 of the post-treatment observational periodT6: After 2 weeks of the post-treatment observational period (scheduled visit): days 15–19 of the post-observational treatment period

Patient symptoms and medication status will be assessed using the electronic patient-reported outcomes (ePRO) system. Patients will download a specialized patient diary app on their smartphones or tablets and respond to the questions. ePRO data will be directly transmitted to the EDC system and can be monitored at any time.

### Plans to promote participant retention and complete follow-up {18b}

As part of the plan to facilitate the retention of participants and full follow-up with patients, the following will be implemented: the significance of the trial and medication compliance will be fully explained, and participants will be asked to come to the hospital according to the study schedule. To reduce the burden on participants, past test results will be made available as part of screening procedures. Payment for cooperation in clinical trials will also be offered to reduce the burden of transportation and other expenses. ePRO will allow participants to enter their “application of Medication and Symptom Diary” using an easy-to-use app on their devices and set reminders on the app for them to enter their logs daily.

### Data management {19}

Investigators will promptly prepare or revise the case report form (CRF) using the EDC system following the input manual. The data described in the CRF must be consistent with data from source documents. If any discrepancy between the source document and CRF exists, the reason for the discrepancy must be explained. Investigators must ensure that the CRF data are accurate and complete. The PI will confirm the adequacy of the prepared CRF content and sign it electronically. Data are stored securely in the study databases and only accessible to research personnel (e.g., investigators, CRCs, monitors, and data managers) trained in confidentiality and privacy procedures.

### Confidentiality {27}

All parties involved should give sufficient consideration to the protection of patients’ personal information and privacy, in accordance with relevant laws and regulations. When investigators report data related to the trial, such as CRFs, patients should be identified by the identification code instead of their names and medical record numbers. When monitors, auditors, clinical trial review committees, and regulatory authorities have direct access to source documents, patients’ privacy should be preserved. Similarly, when disclosing the results of the trial, the patients’ privacy should be preserved. Furthermore, the information obtained in the trial should not be leaked to any third party, except when requested by public authorities.

### Plans for collection, laboratory evaluation, and storage of biological specimens for genetic or molecular analysis in this trial/future use {33}

N/A, as biological data for genetic or molecular analyses will not be collected.

## Statistical methods

### Statistical analysis methods for primary and secondary outcomes {20a}

The analysis of the primary endpoint will be conducted in the full analysis set, which will include all randomized patients who received at least one dose of treatment during the study, data collected after treatment commencement, and adherence to GCP. A one-sided *p*-value < 0.05 will be considered statistically significant. The following closed testing procedure will be used to compare the three groups: the placebo group as the control group, the group with 300 mg/day acotiamide, and the group with 600 mg/day acotiamide.The placebo and acotiamide groups (300 mg/day and 600 mg/day groups will be pooled) will be analyzed using a normal approximation to the binomial distribution test. If the difference is significant, the next step will be followed. Otherwise, the procedure will be terminated.For the acotiamide groups (300 mg/day and 600 mg/day), a normal approximation to the binomial distribution test will be performed.

In addition, regardless of whether significance is observed in 1 and 2 above, the difference in the proportion of patients who improve between the placebo and acotiamide groups and between the two acotiamide groups, and the two-sided 90% confidence interval will be evaluated.

As secondary endpoints are exploratory endpoints, proportions will be analyzed using a normal approximation to the binomial distribution test with the placebo and acotiamide groups. Similarly, the same method will be used to test the 300 mg/day group against the 600 mg/day group. The change from the baseline will be analyzed using analysis of covariance (ANCOVA) with the baseline values, as covariates will be employed to test with the placebo and acotiamide groups. Furthermore, the same method will be applied to test the superiority of the 600 mg/day group over the 300 mg/day group.

SAS software (version 9.4; SAS Institute, Cary, NC, USA) will be used for all analyses.

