### Trial design {8}

The study is an investigator-initiated, multicenter, phase II, double-blind, randomized, placebo-controlled trial with three study arms: acotiamide 300 mg/day, acotiamide 600 mg/day, or a placebo, randomized 1:1:1 and stratified by the institution.

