## Methods: participants, interventions, and outcomes

### Study setting {9}

This study will be conducted at five Japanese institutions with experts in the treatment of EMDs: Kyushu University, Kawasaki Medical School, Nippon Medical School, the National Center for Global Health and Medicine, and Gunma University. Participants will undergo 4 weeks of treatment with acotiamide 300 mg/day, acotiamide 600 mg/day, or a placebo. Then, participants without remission of symptoms will undergo another 4 weeks of treatment with acotiamide 600 mg/day. Forty-two patients will be recruited and followed up for a maximum of 10 weeks. The study protocol was written in accordance with the Standard Protocol Items: Recommendations for Interventional Trials (SPIRIT) statement and approved by the Institutional Review Board (IRB) of Kyushu University for Clinical Trials (IRB No. 2021301; June 28, 2021). The trial was registered in the Japan Registry of Clinical Trials (jRCT; No. jRCT2071210072: October 11, 2021) before patient enrollment. All patients participating in the study will give written consent obtained by the researchers. The flow of the study is illustrated in Fig. 1.

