### Intervention description {11a}

#### Pre-treatment observational period

Participants who consented will be examined and observed to confirm their eligibility during the pretreatment observational period. The maximum duration of the pretreatment observational period will be 28 days after obtaining consent. During this period, participants will complete a “symptom diary” for seven consecutive days out of 10 before enrollment. If any of the drugs listed in the concomitant use prohibition had been used, their use will be discontinued after consent has been obtained. After confirmation of eligibility, the participants will be enrolled and randomized 1:1:1 to receive acotiamide 300 mg/day, acotiamide 600 mg/day, or a placebo.

#### Treatment period 1

Participants will take the assigned drugs three times per day before meals for 4 weeks and complete the “application of Medication and Symptom Diary.” Participants will visit the institution after 4 weeks of treatment in period 1 (day 29; validity period: days 28–32) to undergo pre-defined examinations and observations, including HRM and symptom assessment.

#### Treatment period 2

Participants who complete treatment period 1 will take 200 mg/dose of acotiamide three times per day before meals for 4 weeks in an open-label fashion and complete the “application of Medication and Symptom Diary.” Patients will visit the institution after 4 weeks of treatment in period 2 (day 29; validity period: days 28–32) to undergo pre-defined examinations and observations, including HRM and symptom assessment.

However, if IRP is normalized (less than the standard value of IRP set for each HRM instrument) based on the HRM study and the worst value of the symptom of food sticking in the chest is 0 (elimination case) after 4 weeks of treatment in period 1 (day 29; validity period: days 28–32), participants will not proceed to treatment period 2 but will transfer to the post-treatment observational period.

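### Randomization is stratified by institution, but the stated tests and ANCOVA leave institution out: a valid but somewhat inefficient choice if sites differ (minor)

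*Protocol article*

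**What the plan says.** Trial design {8} describes the arms as "acotiamide 300 mg/day, acotiamide 600 mg/day, or a placebo, randomized 1:1:1 and stratified by the institution". Sequence generation {16a} repeats this: "employing a stratified blocked randomization method stratified by the institution, with a 1:1:1 allocation ratio". Study setting {9} gives the number of strata: "This study will be conducted at five Japanese institutions with experts in the treatment of EMDs".

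Statistical analysis methods {20a} then names the analyses. For the primary comparison of placebo with both active arms combined: "300 mg/day and 600 mg/day groups will be pooled) will be analyzed using a normal approximation to the binomial distribution test". The second step, 300 mg/day against 600 mg/day, uses the same test. For the secondary endpoints, "proportions will be analyzed using a normal approximation to the binomial distribution test with the placebo and acotiamide groups", and for change scores, "The change from the baseline will be analyzed using analysis of covariance (ANCOVA) with the baseline values, as covariates". None of these uses institution as a stratum or covariate. Sample size {14} is also calculated for the unstratified test.

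**The concern.** Blocking within institution balances the arms site by site. If response differs between sites, the true variance of the treatment difference is then smaller than a formula that treats all 42 patients as one sample assumes. A crude test keeps the between-site variation in its standard error. Its p-values are then too large, its 90% intervals too wide, and its real error rate falls below the nominal 5%. The same holds in principle for an ANCOVA without institution.

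This is more than a detail left to an analysis plan that is not shown, because the article commits to a named unstratified test and sizes the trial on it. What is at stake is efficiency in a small trial, not validity.

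**Working it through.** **1. The plan's own sample size.** Inputs from Sample size {14}: placebo 15%, acotiamide 55%, allocation 2:1, one-sided 5%, power 80%.

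- Pooled rate = (0.15 + 2 × 0.55)/3 = 0.4167.
- Null term: √(0.4167 × 0.5833 × 1.5) = 0.6038.
- Alternative term: √(0.15 × 0.85 + 0.55 × 0.45/2) = 0.5012.
- Placebo n = (1.645 × 0.6038 + 0.842 × 0.5012)² / 0.40² = 12.5, rounded up to 13. Total 13 + 26 = 39, as stated.
- Power at 14 + 28 = 42: Φ[(0.40 × √14 − 1.645 × 0.6038)/0.5012] = Φ(1.004) = 84.2%.

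The stated 39 therefore rests on the crude pooled-variance test. The unpooled version gives 30, and the continuity-corrected and two-sided versions each give 51.

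**2. What site differences do.** The setting was simulated with 42 patients at five sites and permuted blocks within site, 40,000 runs per cell. Site effects were a normal random intercept on the logit scale, with overall rates held at 15% and 55%. The crude z test was compared with the site-stratified Cochran-Mantel-Haenszel test, both one-sided at 5%. Site sizes, block size and site SD are assumptions, because the article gives none of them.

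Power, crude v stratified (%):

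| Site sizes, block | SD 0 | SD 0.5 | SD 1.0 | SD 1.5 |
|---|---|---|---|---|
| 9/9/8/8/8, block 3 | 84.7 v 84.0 | 85.3 v 85.4 | 86.0 v 88.3 | 85.9 v 90.8 |
| 9/9/8/8/8, block 6 | 84.8 v 83.6 | 84.9 v 84.7 | 85.7 v 88.0 | 85.7 v 90.6 |
| 22/8/6/4/2, block 3 | 85.2 v 84.0 | 85.2 v 84.8 | 85.2 v 87.0 | 85.3 v 89.5 |
| 22/8/6/4/2, block 6 | 84.8 v 83.2 | 84.8 v 84.1 | 85.4 v 86.9 | 84.8 v 88.6 |

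The gain from stratifying is thus −0.8 to −1.6 points at SD 0, −0.7 to +0.1 at 0.5, +1.5 to +2.3 at 1.0 and +3.8 to +4.9 at 1.5.

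**3. Real size at nominal 5%.** Ranges are over the same four layouts.

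| Common response | SD | Crude | Stratified |
|---|---|---|---|
| 41.7% | 0 | 4.8-5.2% | 4.9-5.1% |
| 41.7% | 1.0 | 3.8-4.1% | 4.8-4.9% |
| 41.7% | 1.5 | 3.2-3.7% | 5.0-5.1% |
| 15% | 1.0 | 3.2-3.3% | 3.4-3.7% |
| 15% | 1.5 | 2.3-2.8% | 3.2-3.5% |

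The 41.7% rows isolate the effect of leaving site out. At 15% both tests are conservative, so much of that shortfall comes from few events.

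**4. What the assumed SDs mean.** With the overall acotiamide rate held at 55%, the logit intercept is 0.21, 0.24 and 0.28 at SD 0.5, 1.0 and 1.5. Taking 1/(1 + exp(−(intercept ± SD))), sites one SD below and above the centre respond in 43% and 67%, 32% and 78%, and 23% and 86% of patients.

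**The case against.** The strongest reply is that nothing in the design fails. Type I error is not inflated. The crude test holds about 84-86% power across these scenarios, against a target of 80%. A worthwhile gain needs large site differences, and the documents give no reason to expect them on the primary endpoint: five expert centres, common eligibility criteria, and a patient-reported diary entered in one app rather than read at the site. At SD 0.5 the gain is nil. Stratifying also has a price. With unequal sites it can cost up to about 1.7 points when sites are alike, and 14 placebo patients over five sites average only 14/5 = 2.8 per site. All of this stands, and it limits the point to a minor one.

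A reader might go further and infer that different manometry instruments distort the manometric endpoints or weaken the planned correlation of integrated relaxation pressure (IRP) with symptoms, because Intervention description {11a} calls IRP normal when "less than the standard value of IRP set for each HRM instrument". The documents do not support that. They state neither how many instruments are in use nor any offset between them. Normalized IRP is already judged against each instrument's own limit. A constant offset cancels in a change score. No method is given for the correlation, so a missing device term there is not an error of this text.

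The reply does not remove the mismatch itself. The article fixes both a stratified randomization and an unstratified test, and the remedy is cheap.

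**Conclusion.** The point holds as a minor efficiency issue. The analyses whose method is stated for proportions and change scores leave out the factor on which randomization is stratified. The primary test stays valid and above its power target, and the loss is only relative to a stratified test. It is nil at an assumed site SD of 0.5 or less, about 2 points at 1.0 and about 4 to 5 at 1.5. The size of the loss depends wholly on the assumed SD, site sizes and block size. No ANCOVA loss was calculated, so there the point rests on principle alone.

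Two stronger readings should be resisted. One is that the trial is underpowered or its error rate inflated; the calculations show neither. The other is that every analysis ignores institution; the article leaves open the method for the correlation and the variables for the exploratory subgroup analyses.

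**What to change.** In Statistical analysis methods {20a}, before unblinding:

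- Make the primary comparison, the 300 v 600 mg/day comparison and the secondary proportions one-sided Mantel-Haenszel tests stratified by institution.
- Report the Mantel-Haenszel-weighted risk difference with a stratified two-sided 90% interval, so that estimate and test agree.
- Add institution to the ANCOVA beside the baseline value.
- State in advance one rule for merging very small sites, applied to both types of analysis. Sites average 42/5 = 8.4 patients.
- Keep the crude normal-approximation test as a sensitivity analysis, which preserves the link to the sample size calculation.

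The change takes a few lines and no new data or patients. Its downside is about 1 to 2 points of power if sites do not differ, which leaves power at about 83-84% for 42 patients, still above 80%.

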### Outcomes {12}

#### Primary endpoint measurement

The primary endpoint is the proportion of patients exhibiting an improvement in symptoms of food sticking in the chest after 4 weeks of treatment period 1.

“Looking back on your day, did you have any troubles with symptoms of food sticking when you swallowed?” Patients will respond to the question on the following six levels:0: No symptoms1: I had symptoms but had no troubles.2: I had symptoms and had some troubles.3: I had symptoms and was moderately troubled.4: I had symptoms and was quite troubled.5: I had symptoms and was extremely troubled.

The percentage of patients showing an improvement in symptoms is defined as the percentage of patients whose worst symptom score in the latest week was 0 (no symptoms) or 1 (symptoms but no troubles) out of the six levels and whose score improved by at least two points.

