### Sample size {14}

The primary analysis will be a comparison of treatment outcomes between the acotiamide (the 300 mg/day and 600 mg/day groups will be pooled) and placebo groups. The secondary analysis will be a comparison of treatment outcomes between the 300 mg/day and 600 mg/day groups to investigate the dose–response to acotiamide. Therefore, the sample size will be set based on a comparison between the acotiamide and placebo groups (allocation ratio 2:1).

In the prospective observational study conducted at Kyushu University Hospital, 10 out of 23 participants (43.5%), who answered the upper abdominal symptom questionnaire (Revised F Scale) after 4 weeks of acotiamide administration (300 mg/day), answered “No” to “Do you feel any symptom of food sticking in the chest (grabbing) when you swallow something?” as a question of the symptoms of food sticking in the chest. Although a scale different from the Revised F Scale will be used to evaluate the efficacy of acotiamide in the current trial, we expect that a similar proportion of patients will show an improvement in symptoms of food sticking in the chest after acotiamide administration. Therefore, we assume that 55% of patients in the acotiamide group will show an improvement in the symptom of food sticking in the chest. In contrast, 15% of patients in the placebo group are assumed to show an improvement in their symptoms. Considering the exploratory nature of this clinical trial, 39 patients are needed to reach a power of 80% for a normal approximation to the binomial distribution with a one-sided significance level of 5%. Considering the possibility of one dropout per group, the target number of participants is set to 42 (14 in each group).

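### The primary test makes no use of the baseline symptom score, although the responder rule depends on it and randomization does not balance it, so a valid test is left exposed to chance imbalance at 14 v 28

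*Protocol article*

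**What the plan says.** - **Primary test** (Statistical analysis methods {20a}): the placebo and pooled acotiamide groups "will be analyzed using a normal approximation to the binomial distribution test". No covariate or stratum is named. In the same section, ANCOVA with the baseline value is planned for the change-from-baseline secondary endpoints only.
- **Responder rule** (Primary endpoint measurement): a patient counts as a responder if the worst score over the last seven days "was 0 (no symptoms) or 1 (symptoms but no troubles) out of the six levels and whose score improved by at least two points".
- **Entry** (Inclusion criteria): a score of 2 or more on at least one screening evaluation, so baseline worst scores of 2 to 5 are possible.
- **Randomization** (Sequence generation {16a}): "employing a stratified blocked randomization method stratified by the institution". Baseline score is not a factor.
- **Sample size** ({14}): the basis is a "comparison between the acotiamide and placebo groups (allocation ratio 2:1"), "with a one-sided significance level of 5"%. For acotiamide, "we assume that 55% of patients in the acotiamide group will show an improvement"; for placebo, "15% of patients in the placebo group are assumed to show an improvement in their symptoms". The result is that "39 patients are needed to reach a power of 80"%, raised to 42 for dropout.

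**The concern.** The two-point rule uses baseline, but that does not adjust for it. It makes the hurdle depend on where the patient starts. If response then varies with the starting score, any chance difference in starting scores between 14 placebo and 28 acotiamide patients passes straight into the crude difference in proportions. The design does nothing to limit that difference, and the planned primary test does nothing to correct for it.

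Two things are at stake. In one direction, a positive result could be put down to more severe patients on placebo. In the other, a real effect could be missed. An adjustment chosen after the baseline table is seen would look data-driven, whereas one fixed now would not.

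**Working it through.** **1. The plan's own figure.** Inputs from the sample size section: p0 = 0.15, p1 = 0.55, ratio 2:1, one-sided 5%, power 80%. The pooled rate is p = (0.15 + 2 × 0.55)/3 = 0.4167.

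n0 = [1.645 × √(p(1−p) × 1.5) + 0.8416 × √(0.15 × 0.85 + 0.55 × 0.45/2)]² / 0.40²
= (0.993 + 0.422)² / 0.16 = 12.5, so 13.

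13 + 26 = 39, which matches. The sample size belongs to the unadjusted test and is not in question.

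**2. The rule applied to each starting score** (reading the improvement as measured from the baseline worst score).

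| Baseline | Final score that counts | Smallest drop |
|---|---|---|
| 2 | 0 only | 2 |
| 3 | 0 or 1 | 2 |
| 4 | 0 or 1 | 3 |
| 5 | 0 or 1 | 4 |

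A patient at 2 faces the strictest end state, and a patient at 5 the largest drop. The hurdle depends on baseline, but which patients respond least is not known.

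**3. Size of chance imbalance.** Assume 40% of patients start at 4–5 (the article gives no figure). The SD of the difference in that share is √(0.4 × 0.6 × (1/14 + 1/28)) = 0.160, or 16 points. With a 50% share it is √(0.25 × 0.1071) = 0.164, and a difference of 20 points or more in either direction arises in about 23% of simulated trials.

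The crude difference shifts by the imbalance times the gap in response between strata. With a 20-point imbalance and assumed response of 5% v 25%, the shift is 0.20 × 20 = 4 points. With 20% v 60% it is 0.20 × 40 = 8 points.

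**4. Simulation.** 200,000 trials per scenario, 14 v 28, 40% at 4–5, odds of response lower at 4–5 by the stated odds ratio (OR), marginal rates held fixed. The crude test is z = (p1 − p0)/√(p(1−p)(1/14 + 1/28)). The stratified test is Mantel-Haenszel (MH), scores 2–3 v 4–5: z = Σ(y − n1·m/N) / √Σ[n0·n1·m(N−m)/(N²(N−1))], where in each stratum y is acotiamide responders, m all responders, n0 and n1 the group sizes and N their sum. An imbalance beyond 0.9 SD occurs in about 16% of trials in each direction.

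One-sided type I error (%):

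| True rate | OR | Crude, all trials | Crude, placebo more severe | Crude, acotiamide more severe | MH, same two subsets |
|---|---|---|---|---|---|
| 15% | 3 | 4.7 | 7.5 | 2.7 | 3.8, 4.4 |
| 15% | 6 | 4.7 | 8.6 | 2.1 | 3.4, 4.6 |
| 15% | 10 | 4.8 | 9.5 | 1.9 | 3.4, 4.7 |
| 30% | 3 | 5.2 | 9.4 | 2.3 | 4.8, 4.7 |
| 30% | 6 | 5.2 | 11.9 | 1.4 | 5.0, 4.9 |
| 30% | 10 | 5.2 | 13.5 | 1.0 | 5.0, 4.9 |

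Power at 15% v 55% (%):

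| OR | Crude, all trials | MH, all trials | Crude, acotiamide more severe | MH, acotiamide more severe |
|---|---|---|---|---|
| 1 | 85.1 | 83.7 | 85.3 | 82.5 |
| 3 | 85.2 | 85.5 | 77.1 | 85.0 |
| 6 | 85.1 | 87.8 | 72.3 | 88.1 |
| 10 | 85.2 | 89.7 | 69.7 | 90.1 |

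**5. A non-monotone case.** Assume equal shares at scores 2/3/4/5, placebo response 10/25/15/5% and acotiamide response 45/70/55/40%. Power is about 84% crude and 83% with either a 2–3 v 4–5 or a 2 v 3-and-above cut. A binary cut that does not follow the true pattern loses about 1.5 points.

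**The case against.** The strongest reply is that nothing here is an error. A pre-specified crude comparison of proportions is a standard choice for a 42-patient phase II trial that calls itself exploratory, and it agrees with the sample size. That stands.

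Three stronger readings are tempting, and the article supports none of them:

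- **That the primary test is biased, or has a 7–14% false-positive rate.** It does not. Randomization balances baseline in expectation, and overall error is about 5% in every scenario. The 7–14% figures apply only to the roughly one trial in six with a marked imbalance favouring acotiamide. The mirror sixth has about 1–3%. Any unadjusted test behaves this way given a prognostic covariate.
- **That adjustment usually adds power.** It does so only if baseline is strongly related to response. At an odds ratio of 3 the two tests are level, and with no relation adjustment loses about 1.5 points.
- **That 2–3 v 4–5 is the right split.** Because a patient at 2 must reach 0, the relation need not be monotone, and 2 v 3-and-above is equally arguable.

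It can also be said that an adjusted sensitivity analysis may sit in the unseen analysis plan, and that the secondary ANCOVA already gives a baseline-adjusted view of the same symptom. Both are fair, and the absence of a sensitivity analysis from the article is not the point. The article does fix the primary test as unadjusted. The ANCOVA addresses a change score, not the responder difference on which the trial's conclusion rests.

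**Conclusion.** The point holds as a weakness of precision and of credibility under imbalance, not of validity. The primary comparison leaves out a score that the trial already collects and that its own responder rule depends on, with only 14 patients on placebo and no balancing of that score.

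The size is conditional on assumptions: a 40% share at scores 4–5, odds ratios of 3 to 10, and common response rates of 15% or 30%. Under these, marked imbalance moves the crude one-sided error from about 5% to about 7–14% or about 1–3% according to direction. When acotiamide draws the more severe patients, crude power falls to about 70–77%, below the 80% target. A stratified test whose cut follows the true pattern stays at about 3–5% error. Averaged over all trials, the effect on power is modest, from about −1.5 to +5 points. If baseline proves unrelated to response, there is nothing to gain. The change is worth making, but the trial does not depend on it.

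**What to change.** Before unblinding, pre-specify a baseline-adjusted primary comparison that reports a test and a risk difference with 90% CI. Either form will do:

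- Mantel-Haenszel with one binary stratum on the baseline worst score, the cut fixed in advance on clinical grounds; or
- a logistic model with baseline score, standardized to a risk difference. This avoids a cut, but a single linear term would still assume a monotone relation.

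Make it the primary analysis, or a named key analysis beside the crude test. Define the baseline worst score explicitly. Keep to one binary stratum: about 28 × 0.55 + 14 × 0.15 = 17.5 responders are expected, and crossing baseline with five institutions would give ten cells for 42 patients.

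The cost is protocol or analysis-plan wording. No new data are needed, since the pre-enrolment diary supplies the score, and no change in sample size. The downside is about 1–2 points of power if baseline does not predict response or the cut is poorly chosen. From about 85% at 14 v 28, that still leaves power above 80%.
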